### Data analysis plans

Prior to analysis, we will produce data summaries including graphical methods to assess data quality, examine central tendencies and distributional assumptions and randomization success. The primary analysis will consist of an unadjusted intent-to-treat hypothesis test using the Andersen-Gill formulation of the Cox proportional hazards model to compare the times to hospitalizations in the two groups; these models properly adjust for the correlation of multiple repeated events within individuals.. We will also estimate multivariate regression models adjusted for the stratification variable and other covariates of interest (such as patient sex, income, race, baseline ejection fraction, and quality of life), retaining these given evidence of confounding or predictive ability. We will employ a confounder selection method based on "change in estimate" criterion. We will assess interaction terms between the a priori potential effect modifiers such as income level, race, and baseline ejection fraction. All hypothesis tests will be two-sided and models will be assessed using standard diagnostic techniques. We will use standard approaches to assess the modeling assumptions and include interaction terms with time if necessary.

Handling of missing data is an important issue in all RCTs. Follow-up data may be missing if participants miss the follow-up visit or withdraw. Even in subjects who are lost to follow-up, however, we will be able to capture any events that result in hospitalization, and thus will still be able to observe our primary outcome. In addition, some subjects may receive a heart transplant during the course of the study. Because the disease trajectory and treatment paradigm change significantly with that event, we will censor patients at the time of transplant; the admission to conduct the transplant will count as an event, but follow-up will cease then and patients will be removed from the risk set. We will compare dropout rates by arm, will attempt to find the reasons for missing data and will compare baseline characteristics in participants with complete vs. incomplete follow-up. In secondary analyses we will investigate the sensitivity to modeling assumptions using imputation models and inverse-probability-weighted estimating equations and models that adjust for informative missing data.

Remote monitoring and behavioral economics in managing patients discharged from the hospital with heart failure: a randomized clinical trial

1623  
1624 A secondary endpoint will be cause-specific rehospitalization, the rationale being that evaluating cause-  
1625 specific hospital admission will allow a more complete understanding of the potential effects of the  
1626 intervention, by indicating how many of the readmissions are due to what cause (e.g., heart failure, MI,  
1627 stroke, other cardiovascular cause, non-cardiovascular cause, etc).  
1628

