1547 over the 24-month enrollment period and follow them for an additional 12 months; with the 1:1  
1548 randomization ratio, we will have 250 control subjects and 250 intervention subjects. The primary  
1549 hypothesis will use a two-sided Type I error rate of 0.05.

1550 Data analysis plans

1551 Prior to analysis, we will produce data summaries including graphical methods to assess data quality,  
1552 examine central tendencies and distributional assumptions and randomization success. The primary  
1553 analysis will consist of unadjusted intent-to-treat hypothesis tests using the logrank test to compare the  
1554 time to hospitalization in the two groups. We will also estimate Cox proportional hazards regression  
1555 models adjusted for the stratification variable and other covariates of interest (such as patient sex,  
1556 income, race, baseline ejection fraction, and quality of life), retaining these given evidence of  
1557 confounding or predictive ability. We will employ a confounder selection method based on "change in  
1558 estimate" criterion. We will assess interaction terms between the a priori potential effect modifiers such  
1559 as income level, race, and baseline ejection fraction. All hypothesis tests will be two-sided and models  
1560 will be assessed using standard diagnostic techniques. We will use standard approaches to assess the  
1561 proportional hazards assumption and include interaction terms with time if necessary. We will also fit  
1562 frailty models to analyze repeated rehospitalizations within patients; these models properly adjust for  
1563 the correlation of multiple events within individuals.

1564 Handling of missing data is an important issue in all RCTs. Follow-up data may be missing if participants  
1565 miss the follow-up visit or withdraw. . Even in subjects who are lost to follow-up, however, we will be  
1566 able to capture any events that result in hospitalization, and thus will still be able to observe our primary  
1567 outcome. We will compare dropout rates by arm, will attempt to find the reasons for missing data and  
1568 will compare baseline characteristics in participants with complete vs. incomplete follow-up. In  
1569 secondary analyses we will investigate the sensitivity to modeling assumptions using imputation models  
1570 and inverse-probability-weighted estimating equations and models that adjust for informative missing  
1571 data.

1572 Cost effectiveness analysis

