## Final Statistical Analysis Plan

### Statistical considerations

Power and sample size issues. Our primary outcome is time to readmission for any cause. The primary comparison will be the times to events compared between the intervention arm and the usual care arm; that is, the primary hypothesis is whether a series of interventions, adapted to the behavior and outcomes of each particular patient, will reduce readmission rates compared to usual care.

We expect the 1-year event rate to be 47% in the usual care arm based on data obtained on our target population at UPHS. We wish to have 80% power to detect an absolute decrease in this rate of about 10% in the intervention group; this corresponds to a hazard ratio of 0.73. We will accrue 566 patients over the 24-month enrollment period and follow them for an additional 12 months; with the 1:1 randomization ratio, we will have approximately 283 subjects in each arm. The primary hypothesis test will use a two-sided Type I error rate of 0.05. Note that the power calculations are based on the time to first readmission; if patients experience multiple readmissions, statistical power will be increased.

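### The primary Andersen-Gill model does not by itself adjust for within-patient correlation, and the plan names no patient-clustered variance or frailty term for the primary test

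*Supplement*

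**What the plan says.** The final SAP, under Data analysis plans, defines the primary analysis as an "unadjusted intent-to-treat hypothesis test using the Andersen-Gill formulation" of the Cox model, counting all hospitalizations. Its only provision for repeat events in one patient is the statement that "these models properly adjust for the correlation of multiple repeated events within individuals". Section 10 of the final protocol carries the same statement. Under Statistical considerations the test is given a "two-sided Type I error rate of 0.05". The power calculation there is based on first readmissions, and the plan adds that repeat readmissions would raise power.

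Neither document names a robust or sandwich variance, clustering on patient, or a random effect for the primary test. The bootstrap is confined to the cost-effectiveness analysis. The inverse-probability-weighted estimating equations belong to secondary sensitivity analyses. Ejection fraction, income, quality of life and other covariates enter only the additional adjusted models.

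**The concern.** The Andersen-Gill partial likelihood treats a patient's successive events as independent given the covariates. Treatment arm is the only covariate in the primary model, so any difference between patients in underlying readmission rate becomes within-patient correlation that the model-based standard error ignores. Each repeat admission then counts as fresh information, the confidence interval is too narrow and the test rejects too often.

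The quoted sentence matters because it tells the analyst that the problem is already solved. Someone who follows it literally has no reason to add clustering; someone who knows the usual practice will add it. Both would comply with the text and could report different p-values and intervals for the one primary test. The final protocol describes the study as open-label, which is a further reason to settle this before the data are examined.

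**Working it through.** **Inputs from the documents.** "We expect the 1-year event rate to be 47% in the usual care arm"; "this corresponds to a hazard ratio of 0.73"; "We wish to have 80% power"; 566 patients, about 283 per arm; two-sided alpha 0.05; 24 months of accrual plus 12 months; 12 months of participation per patient.

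**Input not in the documents.** The between-patient variance of the readmission rate. I assume a gamma frailty with mean 1 and variance θ, and show θ from 0.1 to 3.

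**1. The plan's own figure.**
- ln(0.63)/ln(0.53) = 0.728, which agrees with 0.73.
- Events needed (Schoenfeld): 4(1.960 + 0.842)²/(ln 0.73)² = 317.
- With exponential times, uniform 24-month accrual and a common close 12 months later, the event probabilities are 0.700 and 0.590. Then 566 patients give 283 × (0.700 + 0.590) ≈ 365 first events and 85.2% power. After an 11.7% loss (1 − 500/566) power is 80.6%. The stated 80% is reproduced.
- This is a first-event calculation and involves no correlation between repeat events.

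**2. Variance inflation under no treatment effect.** Over 12 months, a patient with frailty w has a Poisson count with mean wμ.
- P(no readmission) = (1 + θμ)^(−1/θ) = 0.53, so 1 + θμ = 0.53^(−θ).
- The variance-to-mean ratio of the counts is 1 + θμ, and the model-based variance is too small by this factor.
- Type I error = 2[1 − Φ(1.96/√(0.53^(−θ)))].

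Example, θ = 1: 0.53^(−1) = 1.887; 1.96/√1.887 = 1.427; type I error 15.4%.

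**3. Check by simulation.** Andersen-Gill fits, 283 per arm, 4,000 trials per setting. The Monte Carlo standard error near 5% is √(0.05 × 0.95/4000) = 0.34 points.

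| θ (assumed) | Mean readmissions per patient-year | Variance inflation | Type I, model-based, formula | Type I, model-based, simulated | Type I, clustered, simulated |
|---|---|---|---|---|---|
| 0.1 | 0.655 | 1.07 | 5.8% | 6.5% | 5.5% |
| 0.25 | 0.688 | 1.17 | 7.0% | 6.8% | 4.9% |
| 0.5 | 0.747 | 1.37 | 9.5% | 9.0% | 5.0% |
| 1 | 0.887 | 1.89 | 15.4% | 16.1% | 5.2% |
| 1.5 | 1.061 | 2.59 | 22.3% | 22.1% | 4.6% |
| 2 | 1.280 | 3.56 | 29.9% | 28.9% | 4.9% |
| 3 | 1.906 | 6.72 | 45.0% | 45.3% | 5.7% |

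With 10% additional censoring, the model-based simulated values are 9.3%, 14.2% and 29.9% at θ = 0.5, 1 and 2.

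**4. Power with the clustered variance.** At a rate ratio of 0.73 and 12 months per patient, simulated power is about 78% (θ = 0.25), 73% (0.5), 68% (1) and 60% (2). Across these settings the mean number of readmissions rises from 0.69 to 1.28 while power falls, so more repeat events do not of themselves mean more power.

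**The case against.** The strongest reply is that the plan never says model-based errors will be used. Its declared aim is to account for the correlation, and an analyst who pursues that aim will cluster on patient and keep the 5% level. The sentence can be read as shorthand for Andersen-Gill with clustered errors. Part of this stands: a reader might infer from the plan that the primary test will have an inflated error rate, and the documents do not support that. They are silent on the variance. What remains is that the sentence credits the model with a property it lacks, and that the variance is left open.

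The second reply is that the error rates depend on θ. This also stands. A reader might settle on a range such as 9% to 30%, but that corresponds to θ from 0.5 to 2, and nothing in the documents selects those values. Nor do they report that readmissions concentrate in a minority of patients. With weak heterogeneity (θ of 0.25 or less) the excess is only one or two percentage points.

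The commitments to check modeling assumptions and to run weighted sensitivity analyses are useful, but they do not specify the variance of the primary test. The original SAP used similar words about frailty models. That change is not a fault in itself, and this point rests on the final text alone.

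**Conclusion.** The point holds as a wrong justification combined with a missing specification. It does not show that the trial will use an invalid test. If model-based errors are used, the stated level is exceeded for every θ above zero, because 0.53^(−θ) is then greater than 1. The error runs from about 6% at θ = 0.1 to about 45% at θ = 3, and the correct interval on the log scale is wider than the model-based one by √1.37 = 1.17, √1.89 = 1.37 and √3.56 = 1.89 times at θ = 0.5, 1 and 2. With clustering on patient, the level is about 5%.

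These sizes assume a gamma frailty, a constant rate over 12 months and the plan's 47%. The missing variance statement can be read directly from both documents and depends on none of these assumptions. Because it concerns the validity of the sole primary test, it should be corrected before that test is run.

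**What to change.** In the final SAP (Data analysis plans) and section 10 of the final protocol, replace the sentence with: *The primary test is the Wald (or score) test from the unadjusted Andersen-Gill model using a robust sandwich variance clustered on patient; all confidence intervals use that variance.* One of Wald or score should be chosen. Use the same variance in the adjusted model and in any cause-specific analysis that counts repeat admissions; the documents do not make clear whether the cause-specific analysis does.

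Qualify the remark about repeat readmissions and power: the gain depends on how much patients differ, and it should be worked out with the clustered variance and a stated range for θ.

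The cost is one sentence in each document and one option in the code. Intervals will be wider than the naive model gives. The power figures above fall below 80%, but not all of that shortfall comes from the variance: they assume 12 months per patient, whereas the plan's 80% is reproduced only with follow-up to a common close. That mismatch is a separate matter.

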#### 1629 Cost effectiveness analysis

1630 To assess the cost-effectiveness of the interventions, we will use analytic methods for economic  
1631 evaluations in clinical trials. Our approach will be similar to Specific Aim 3 using cost as the outcome. We  
1632 will use generalized linear models to adjust for the stratification variable and other factors. Cost-  
1633 effectiveness ratios will be calculated as the difference in costs divided by the difference in  
1634 rehospitalization rate calculated under Specific Aim 3 for the “within-trial” analysis, with parametric 95%  
1635 CIs for the cost per percentage point increase in adherence and acceptability curves. Standard errors  
1636 and the correlation of the difference in cost and effect will be obtained using a bootstrap procedure. A  
1637 further cost-effectiveness analysis from the “societal perspective” will be conducted to assess the  
1638 impact of the rehospitalization rate reductions measured as cost per QALY gained. To address  
1639 uncertainty in the micro simulation model, we will also conduct a probabilistic sensitivity analysis  
1640 (PSA) by defining probability distributions for the variables in the model used to calculate costs and  
1641 effectiveness. We will use the results of the PSA to calculate confidence (or credible) intervals and  
1642 acceptability curves.

1643

#### 1644 **Summary of statistical analysis plan changes**

1645 There were three amendments to the Data Analysis plan, motivated by an evolving understanding of  
1646 disease management pathways for heart failure patients that impacted how to accurately measure the  
1647 intervention’s effectiveness. The first amendment to the Data Analysis plan in November of 2016 was  
1648 motivated by the addition of censoring criteria for enrolled patients who received an LVAD or transplant  
1649 during study period because the disease trajectory and treatment paradigm change significantly with  
1650 these events. It was determined these patients should be censored at the time of LVAD or transplant.  
1651 The decision to include censoring criteria led to increasing the sample size from 500 to 566 when it was  
1652 determined the censoring rate was higher than expected. The second amendment to the Analysis plan  
1653 in April 2017 clarifies that the Anderson-Gill formulation of the Cox proportional hazards model will be  
1654 used to account not just for time to first admission, but also repeated events within individuals to  
1655 accurately measure the impact of all admissions at the individual level over the course of the  
1656 intervention. The third amendment was in April 2020 and added a secondary endpoint of cause-specific  
1657 rehospitalization, the rationale being that evaluating cause-specific hospital admission will allow a more  
1658 complete understanding of the potential effects of the intervention, by indicating how many of the  
1659 readmissions are due to what cause (e.g., heart failure, MI, stroke, other cardiovascular cause, non-  
1660 cardiovascular cause, etc).
